### Intervention description {11a}

Both groups will receive the ICU-VR intervention during the study period, 3 (early) and 6 (late) months after hospital discharge. ICU-VR (duration: ±14 min) comprises several modules explaining the aspects of ICU treatment that are known to be the most frightening [24, 35]. The content was previously determined by a multidisciplinary team and has been demonstrated to be safe [32, 33]. For COVID-19 ICU survivors, we adapted the latter module by adding additional COVID-19 specific aspects of ICU treatment (i.e. mechanical ventilation in prone position, tracheostomy and isolation measures). In addition, information regarding SARS-CoV-2 and COVID-19 was added, and the voice-over was changed accordingly. Real ICU nurses and physicians were used to re-enact a typical day/treatment for a mock patient undergoing ICU treatment for COVID-19.

ICU-VR is hospital-specific, to expose patients to the actual environment where they were treated. As such, each hospital has its unique ICU-VR. An overview of the ICU-VR intervention of the Erasmus MC is depicted in Fig. 1, and the film script can be found in Additional file 1 (translated from Dutch to English). The intervention will be watched via head-mounted display (HMD-)VR glasses (Oculus Go, Irvine, CA, www.oculus.com/go), and patients will be allowed to move their head freely as to experience all aspects of the virtual environment.

**Fig. 1 Fig1:**
[figure not shown]
Impression of the COVID-19 ICU-VR intervention. Screenshots of the COVID-19 ICU-VR intervention; the ICU physician and nurse welcome the patient while standing in front of the ICU (**a**, left), where the patients are virtually installed in an ICU bed (**a**, right). After the ICU physician and nurse have brought the patient to the ICU room while walking over the ICU, the patient will be placed in the ICU room (**b**, left), where the patient receives an explanation about the surveillance monitor (**b**, right; **c**, left), intubation (**c**, right), prone positioning (**d**, left), drips and infuses (**d**, right), tracheotomy (**e**, left), isolation and personal protection measures (**e**, right), the treatment team (**f**, left) and SARS-CoV-2/COVID-19 (**f**, right). A full overview of the content of the COVID-19 ICU-VR intervention can be found in Additional file 1

### Criteria for discontinuing or modifying allocated interventions {11b}

Not applicable. Patients undergo ICU-VR once in the hospital. As such, discontinuation or modification of the allocated intervention is not possible.

### Strategies to improve adherence to interventions {11c}

Not applicable. Patients undergo ICU-VR once in the hospital. No further adherence is needed.

### Relevant concomitant care permitted or prohibited during the trial {11d}

Participants randomized to the late ICU-VR group require an additional visit to an outpatient clinic to receive ICU-VR. No additional alterations to usual care pathways, including the use of any medication, are required for participants in this study.

### Provisions for post-trial care {30}

Due to the absence of anticipated harm of participation in this study, the accredited medical ethics committee has granted dispensation from the statutory obligation to provide insurance to participants through injury or death caused by the study. The sponsor has a liability insurance which is in accordance with national legislation. Participants will not be compensated for their participation in the study.

### Outcomes {12}

The primary outcome is the effect of early ICU-VR on psychological well-being, expressed as symptoms of PTSD, anxiety and depression and quality of life up to 6 months after hospital discharge. Secondary outcomes are, firstly, the intra-group changes in psychological well-being and quality of life and the inter-group differences in psychological well-being and quality of life during follow-up up to 12 months after hospital discharge, and secondly, patients’ satisfaction with and rating of ICU care and aftercare and patients’ perspectives on ICU-VR.

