**Methods:**

In this multicentre, randomized controlled trial, we aim to examine whether COVID-19-specific ICU-VR, offered 3 months after hospital discharge, improves psychological well-being and quality of life. Secondary objectives are, firstly, to examine the intra-group changes in psychological well-being and quality of life and the inter-group differences in psychological well-being and quality of life during follow-up, up to 12 months after hospital discharge, and secondly, to examine patients’ satisfaction with and rating of ICU care and aftercare and patients’ perspectives on ICU-VR. Eighty adult patients treated for COVID-19 in the mixed-surgical ICUs of four hospitals in Rotterdam, the Netherlands, will be included and randomized (1:1) to either early or late ICU-VR between June 29 and December 31, 2020. Patients randomized to early ICU-VR will receive the ICU-VR intervention during an outpatient clinic visit 3 months after hospital discharge, whereas patients randomized to late ICU-VR will receive ICU-VR 6 months after hospital discharge. Primary outcomes of this study are psychological well-being, assessed using the Impact of Event Scale–Revised (IES-R) and the Hospital Anxiety and Depression Scale (HADS), and quality of life, assessed using the European Quality of Life 5 Dimensions (EQ-5D) and RAND-36 questionnaires, up to 6 months after hospital discharge.

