### Sample size {14}

In the previously conducted pilot study examining the feasibility, safety and clinical relevance of ICU-VR in sepsis survivors, we identified an effect size Cohen’s *d* of 0.77 [33]. Due to the non-normality of PTSD scores after 6 months, these calculations could represent an overestimation of the sample size. We consider the effect estimates for the ICU-VR module to be similar to the intervention group, as was tested in our pilot study. A G*Power analysis revealed that 80 patients have to be included in the study to detect such an effect size, using a two-sided alpha of 0.05, a power of 0.80, a 1:1 randomization and an expected loss to follow-up of 20% based on our pilot study. We will include patients from June 2020 to December 2020. When the minimum required number of patients is reached prior to December 2020, inclusion will be continued until December 2020. When the minimum required number of patients is not reached in December 2020, inclusion will be continued until the minimum required sample of 80 patients is reached.

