## Data collection and management

### Plans for assessment and collection of outcomes {18a}

Psychological well-being will be expressed as the presence and severity of PTSD, anxiety and depression, which will be assessed using the Impact of Event Scale-Revised (IES-R) and Hospital Anxiety and Depression Scale (HADS) [36, 37]. Quality of life will be assessed using the European Quality of Life 5-dimensions (EQ-5D) and RAND-36 questionnaires [38, 39]. Patients’ satisfaction with and rating of ICU care and aftercare and patients’ perspectives on ICU-VR will be assessed using a novel questionnaire.

The IES-R comprises 22 items, assesses subjective distress caused by a traumatic event and has been previously validated in ICU survivors [40]. The IES-R yields a total score (ranging from 0 to 88, with higher scores indicating more severe symptoms), and subscale scores can be calculated for symptoms of intrusion, avoidance and hyperarousal. An IES-R sum score ≥ 24 will be considered as PTSD [41]. The HADS comprises 14 items and is commonly used to determine the levels of anxiety and depression that a patient is experiencing. Seven of the items relate to anxiety and seven relate to depression. A sum score above 8 on either the depression or anxiety subscale will be classified as depression and anxiety, respectively [36].

The EQ-5D measures quality of life in five dimensions (mobility, self-care, usual activities, pain/discomfort and anxiety/depression), from which the weight of a health state can be computed, the EQ-5D utility score, ranging from − 0.446 (worst quality of life) to 1.000 (best quality of life) [42]. Additionally, patients score their current subjective health on a visual analogue scale (EQ-VAS), ranging from 0 (worst health imaginable) to 100 (best health imaginable). The RAND-36 is a 36-item, patient-reported survey of patient health and quality of life. The RAND-36 consists of eight scaled scores, which are the weighted sums of the questions in their section. Each scale is directly transformed to a scale ranging from 0 to 100 on the assumption that each question carries an equal weight. The eight sections are vitality, physical functioning, bodily pain, general health perception, physical role functioning, emotional role functioning, social role functioning and mental health [39].

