## Statistical methods

### Statistical methods for primary and secondary outcomes {20a}

Baseline demographics and treatment-related characteristics will be quantified using descriptive statistics. Continuous variables will be presented as medians (95% range). Categorical variables will be presented as absolute numbers and relative frequencies.

Differences between study groups in continuous variables, such as the IES-R sum score, the HADS anxiety and depression scores, the RAND-36 subscales and the EQ-5D utility score, at several follow-up time points will be analysed using a mixed effect linear regression model with a random intercept for each study site. Patients will also be categorized based on clinically meaningful cut-offs for the IES-R sum score and the HADS anxiety and depression scores. An IES-R sum score ≥ 24 will be considered as clinically relevant PTSD; a HADS anxiety or depression score > 8 will be considered as clinically relevant anxiety or clinically relevant depression, respectively [36, 41, 46]. Differences in categorical variables between study groups at several follow-up time points will be analysed using a mixed effect logistic regression model with a random effect for each site. Differences in continuous or categorical variables throughout follow-up will be analysed using a mixed effect linear or logistic regression model with an interaction variable of time*randomization and a random intercept and/or slope for each individual and each study site as appropriate.

To determine whether there are time-specific windows of opportunity (3 or 6 months after hospital discharge) for the effect of ICU-VR, we will analyse psychological impairments and quality of life 1 month (4 and 7 months after hospital discharge in the early and late intervention groups, respectively), 3 months (6 and 9 months after hospital discharge in the early and late intervention groups, respectively) and 6 months after receiving ICU-VR (nine and 12 months after hospital discharge in the early and late intervention groups, respectively) using mixed effect linear/logistic regression models with a random intercept for each site and an interaction variable time*randomization.

All data will be gathered using Castor EDC. All analyses will be performed using SPSS (version 24.0; SPSS Inc., Chicago, IL) and R for Statistics (R Foundation for Statistical Computing, Vienna, Austria, 2015). A *P* value ≤ 0.05 will be considered statistically significant.

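### PTSD, anxiety, depression and quality of life are jointly primary at an unadjusted 0.05 with no score, time or model singled out, while the 80 patients are sized for one comparison

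*Protocol article*

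**What the plan says.** Outcomes {12} defines the primary outcome in one sentence: "The primary outcome is the effect of early ICU-VR on psychological well-being, expressed as symptoms of PTSD, anxiety and depression and quality of life". The window for it closes at the 6-month assessment. The Abstract assigns instruments without ranking them. For the psychological part: "Primary outcomes of this study are psychological well-being, assessed using the Impact of Event Scale–Revised (IES-R) and the Hospital Anxiety and Depression Scale (HADS". For the quality-of-life part: "assessed using the European Quality of Life 5 Dimensions (EQ-5D) and RAND-36 questionnaires, up to 6 months after hospital discharge".

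Plans for assessment {18a} lists the scores. The IES-R gives one total and the HADS gives an anxiety and a depression subscale. The EQ-5D gives a utility and a VAS. For the last instrument, "The RAND-36 consists of eight scaled scores, which are the weighted sums of the questions in their section"; no summary score is named.

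Statistical methods {20a} names the IES-R, both HADS scores, the RAND-36 subscales and the EQ-5D utility as examples of continuous variables to be compared between groups at several time points. It repeats the IES-R and both HADS scores as dichotomies and adds a longitudinal model with a time-by-randomization interaction. One threshold covers everything: a P value of 0.05 or less "will be considered statistically significant".

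Sample size {14} uses one Cohen's d of 0.77 from the sepsis pilot, a two-sided alpha of 0.05, power 0.80, 1:1 allocation and 20% loss to follow-up, giving 80. It does not name the score behind d. The next sentence reads: "Due to the non-normality of PTSD scores after 6 months, these calculations could represent an overestimation of the sample size".

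**The concern.** Choosing the primary endpoint and its time is a protocol decision. The article makes that decision by declaring several instruments primary at once. It then applies a single-test threshold to each of them and a single-test sample size to the trial.

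Two things are at stake. First, the conclusion that ICU-VR improves psychological well-being and quality of life could be drawn from whichever score, visit or model reaches 0.05, for example one RAND-36 scale at 4 months. Second, no effect size is stated for any other score, so the 80% power cannot be attached to the remaining primary outcomes. The trial is open-label and every primary score is patient-reported, so a rule fixed in advance matters more here than in a blinded trial.

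**Working it through.** **1. The plan's own figure.** Inputs from Sample size {14}: d = 0.77, two-sided alpha 0.05, power 0.80, 1:1, 20% loss. The Limitations section adds that no distribution was assumed. I read this as a Wilcoxon–Mann–Whitney test at its minimum relative efficiency of 0.864; the article does not name the test.

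- Noncentrality with 32 per arm: 0.77 × √(32 × 0.864 / 2) = 2.86. Power is 0.803; with 31 per arm it is 0.790.
- 2 × 32 = 64 evaluable, and 64 / 0.8 = **80**, as stated.
- A t test would need 28 per arm: 56 / 0.8 = 70.

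So 80 is correct for one comparison at an unadjusted 0.05.

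**2. Count of primary comparisons.**

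- Scores named in {20a}: IES-R 1 + HADS 2 + RAND-36 8 + EQ-5D utility 1 = 12. The EQ-VAS, described in {18a}, makes 13.
- Visits: Participant timeline {13} sends questionnaires at 3 months (before the first visit, so before randomization), 4 and 6 months. Two fall after randomization and within the primary window.
- Tested separately at each visit: 13 × 2 = 26. One longitudinal test per score would give 13. The three dichotomies are extra.

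**3. Chance of at least one false positive if any one test suffices.** For k independent tests it is 1 − 0.95^k: 0.185 for k = 4, 0.487 for k = 13 and 0.736 for k = 26. These scores are correlated, so I simulated multivariate normal test statistics with no true effect and counted draws with any |z| > 1.96 (at least 200,000 draws). The equal between-score correlation r, and the between-visit correlation of 0.7, are assumptions.

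| Tests | r = 0.7 | r = 0.5 | r = 0.3 |
|---|---|---|---|
| 4 domains, one visit | 13% | 16% | 17% |
| 12 scores, one visit | 23% | 32% | 40% |
| 13 scores, one visit | 24% | 33% | 42% |
| 13 scores, both visits | 37% | 50% | 60% |

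**4. If both domains must succeed.** With one named score per domain, each tested at 0.05, the joint error is at most 5%. Joint power is lower than single power. Even if both scores had power 0.80, which the article does not show for quality of life, joint power is guaranteed only to be at least 1 − 0.20 − 0.20 = 0.60. It is 0.80 × 0.80 = 0.64 if the two tests are independent.

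**5. Cost of adjusting instead of choosing.** Power per test at d = 0.77 with 32 per arm:

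| Alpha | Distribution-free | t test |
|---|---|---|
| 0.05 | 0.80 | 0.86 |
| 0.05 / 4 = 0.0125 | 0.61 | 0.69 |
| 0.05 / 13 = 0.0038 | 0.44 | 0.53 |

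On the distribution-free basis, restoring power 0.80 with 20% loss would need 115 patients for four domains (2 × 46 / 0.8) or 143 for 13 scores (2 × 57 / 0.8, rounded up).

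**The case against.** Several limits on this point stand.

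- **A statistical analysis plan or full protocol may hold a hierarchy.** It may, and the absence of an adjustment in an article is not in itself a fault. But the joint primary outcome, the blanket threshold and the unadjusted sample size are all stated here, and a later adjustment would not fit the 80 patients.
- **A reader might infer that a false-positive primary result is likely.** The figures do not support that. For 13 scores only the weakest correlation at both visits puts the rate clearly above one half, and every correlation is assumed. What can be shown is strong inflation.
- **A reader might take 13 scores, or 26 tests, as a minimum.** The analysis section names 12 scores, and only as examples. The longitudinal model could give one test per score over the window. That would reduce tests across visits but not across scores.
- **The primary objective joins well-being and quality of life with the word and.** If both are required, the inflation in step 3 does not arise in that form. The article does not state such a rule, nor how many scores would make a domain a success.
- **A reader might take the trial to be sized on the IES-R at 6 months.** The text only implies a PTSD score. In the pilot ICU-VR was given about 8 days after ICU discharge, so its 6 months need not be this trial's 6 months after hospital discharge.

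**Conclusion.** The concern holds in this form: the primary claim has no defined error rate, and the stated 5% and 80% belong to one unadjusted comparison. Under an any-one-score rule the false-positive chance is about 24–42% for 13 scores at one visit and 37–60% at both, for assumed correlations of 0.7 to 0.3. Even the reading most favourable to the plan, four domain tests at one visit, gives 13–17%. Under a both-domains rule the problem moves from error to power. The result does not depend on counting the EQ-VAS, or on which score lies behind d = 0.77. It should be settled before analysis.

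**What to change.** Name one primary endpoint, one time point and one model, tested at 0.05. The IES-R sum score at 6 months is the choice closest to the sample-size text; the sponsor should first confirm that d = 0.77 came from a PTSD score. Make HADS anxiety and depression, EQ-5D and RAND-36 secondary, tested in a fixed order or with Holm's procedure. Report 4-month results and the dichotomies as supportive estimates with confidence intervals.

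Do this before the analyst receives the allocation codes or any between-group comparison is run. Patients and investigators already know the allocation; under Blinding {17a} only the analyst works from coded groups.

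The cost is an amendment and matching registry wording, with no extra patients. Quality of life loses its primary status. Recruitment ended on February 3, 2021 and the trial is open-label, so a choice made now carries some selection risk of its own. The amendment should be dated and should state that no between-group results had been seen.

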### Participant timeline {13}

Figure 2 depicts participants’ recruitment and randomization, the study procedures and the outcomes of the study. Patients admitted for COVID-19 to the ICU of the participating hospitals will be invited to a post-COVID-19 outpatient clinic 3 months after hospital discharge as part of the regional standard of care. All patients will receive an information letter and will be contacted by telephone to discuss participation 1 month prior to this visit. During the outpatient clinic visit, informed consent will be obtained and patients will be randomized. Patients randomized to the early ICU-VR group will receive ICU-VR during the same visit, whereas patients randomized to the late ICU-VR group will receive ICU-VR during a second outpatient clinic visit 3 months later (i.e. 6 months after hospital discharge). Questionnaires will be sent at 3 months (prior to the first outpatient clinic visit), 4 months, 6 months (prior to the second outpatient clinic visit for patients in the late intervention group), 7 months and 12 months after hospital discharge.

**Fig. 2 Fig2:**
[figure not shown]
Flow diagram of the study. Abbreviations: COVID-19, coronavirus disease 2019; EQ-5D, European Quality of life 5 dimension questionnaire; HADS, Hospital Anxiety and Depression Scale; ICU, intensive care unit; ICU-VR, intensive care unit-specific virtual reality; IES-R, Impact of Event Scale–Revised. Eligible patients will be invited to a post-COVID outpatient clinic and randomized across the early and late ICU-VR group. The early group will receive the ICU-VR intervention during the same visit, while the late group receives ICU-VR during a second outpatient clinic visitation 6 months after hospital discharge. Psychological well-being and quality of life will be assessed 3, 4, 6, 7 and 12 months after hospital discharge using follow-up questionnaires

### Sample size {14}

In the previously conducted pilot study examining the feasibility, safety and clinical relevance of ICU-VR in sepsis survivors, we identified an effect size Cohen’s *d* of 0.77 [33]. Due to the non-normality of PTSD scores after 6 months, these calculations could represent an overestimation of the sample size. We consider the effect estimates for the ICU-VR module to be similar to the intervention group, as was tested in our pilot study. A G*Power analysis revealed that 80 patients have to be included in the study to detect such an effect size, using a two-sided alpha of 0.05, a power of 0.80, a 1:1 randomization and an expected loss to follow-up of 20% based on our pilot study. We will include patients from June 2020 to December 2020. When the minimum required number of patients is reached prior to December 2020, inclusion will be continued until December 2020. When the minimum required number of patients is not reached in December 2020, inclusion will be continued until the minimum required sample of 80 patients is reached.

### Recruitment {15}

Patients will receive information 1 month prior to the post-COVID outpatient clinic visit and will be recruited during the post-COVID outpatient clinic visit, after being given the opportunity to ask questions regarding participation.

## Assignment of interventions: allocation

### Sequence generation {16a}

Patients will be randomly assigned to either early ICU-VR, receiving the intervention 3 months after discharge, of late ICU-VR, receiving the intervention 6 months after hospital discharge. Randomization will be a 1:1 allocation as per computer-generated randomization schedule stratified by site using permuted blocks of random sizes. The block sizes will not be disclosed, to ensure concealment.

### Concealment mechanism {16b}

Patients will be randomized using the Castor Electronic Data Capture system (Castor EDC, https://www.castoredc.com, Amsterdam, the Netherlands), an online data capture system including a central randomization service.

### Implementation {16c}

After informed consent has been obtained, patients will be randomized by the principal investigator of each study site using Castor EDC during the post-COVID outpatient clinic at 3 months after hospital discharge. After randomization, Castor EDC reveals the allocation of the patient, where after the patient will receive ICU-VR if allocated to early ICU-VR, or will be invited to a second outpatient clinic 6 months after hospital discharge if allocated to late ICU-VR.

